# Improved oral health in head and neck cancer survivors (OHHNC study): a study protocol for a multicentre two-armed randomised controlled trial

**DOI:** 10.1186/s12885-026-16865-8

**Published:** 2026-09-07

**Keywords:** Head and neck cancer, Oral health, Patient-reported outcome measures, Rehabilitation

## Abstract

**Background:**

Head and neck cancer comprises a heterogeneous group of tumours affecting anatomical sites of the upper aerodigestive tract. Treatment often involves surgery and either radiotherapy or chemoradiotherapy. These treatments are associated with substantial morbidity and may have long-lasting adverse effects on oral health. Oral complications can negatively affect health-related quality of life, nutritional status, and social and work-related functioning. The aim is to evaluate an oral health care programme designed to prevent or mitigate late oral sequalae, and to assess its impact on health-related quality of life, oral health, work ability, nutritional status, healthcare-related economic costs, and psychological well-being.

**Methods:**

This is a study protocol for a Swedish multicentre, two-armed, superiority randomised controlled trial that has been ethically approved by the Swedish Ethical Review Authority. Patient inclusion commenced in September 2025, with an intended sample of 300 participants. Adult patients (≥ 18 years) planned for curative-intent treatment for head and neck cancer (oral cavity, oropharynx, larynx stage III and IV, hypopharynx, nasopharynx, salivary gland, or unknown primary) are randomised (1:1) to either an oral health care programme (intervention) or standard of care. Exclusion criteria: severe alcoholism, cognitive impairment, or inability to understand the Swedish language. Participants are followed before the start of cancer treatment and at 4 follow-ups: 6 months after completion of treatment, and 1, 2, and 3 years after the 6-month follow-up. The primary outcome measure is health-related quality of life. Secondary outcomes include quantitative oral health indicators, return to work, nutritional status, healthcare-related economic costs, and patient-reported outcome measures focusing on self-reported oral health and psychological well-being (depression, anxiety and stress), and self-efficacy.

**Discussion:**

Oral health follow-up for head and neck cancer survivors often lacks consistency and uniformity. To date, few oral health care interventions for head and neck cancer survivors have been evaluated within the framework of a randomised controlled trial. The findings have the potential to inform clinical practice and contribute to the development of more integrated, evidence-based oral healthcare strategies within routine follow-up for head and neck cancer survivors, with the overarching goal of improving their oral health and long-term quality of life.

**Trial registration:**

ClinicalTrials.gov NCT07173270, date 15/9/2025.

**Graphical Abstract:**

**Figure Figa:**
[figure not shown]
Created in BioRender. [name] (2026) https://BioRender.com/q3ajqtm

**Supplementary Information:**

The online version contains supplementary material available at https://doi.org/10.1186/s12885-026-16865-8.

## Background

Head and neck cancer (HNC) consists of a diverse group of tumours affecting anatomical sites of the upper aerodigestive tract, including the oral cavity, pharynx, larynx, nasal cavity, paranasal sinuses, and salivary glands [1, 2]. Treatment of HNC may be given as a single modality, but often requires a multimodal approach using surgery and adjuvant radiotherapy (RT) or chemoradiotherapy (CRT) [2]. The ultimate goal is to achieve cancer cure while keeping treatment-related morbidity to a minimum. However, given the many vital functions of the upper aerodigestive tract, treatment of HNC subsequently impacts patients’ functional capacity, well-being, and quality of life. Although treatment-related morbidity in HNC is complex and diverse, our particular focus here is on the challenges and symptoms related to the oral cavity, and more specifically, in relation to oral health status.

Despite efforts being made to deliver the prescribed irradiation dose volume to the tumour while minimising exposure to surrounding normal tissue, complete avoidance of irradiation to healthy tissue is not possible, which consequently leads to both acute and late treatment sequelae. Oral mucositis is a common acute treatment side effect of RT that subsequently progresses over the course of RT from mild (oral soreness, erythema) to severe (ulcerations) [3, 4]. The peak of oral mucositis is often observed near the end of RT treatment and usually resolves within a couple of months after completion [5]. Further, irradiation of the salivary glands may lead to hyposalivation [3] and possible permanent salivary gland hypofunction [6]. RT may also induce significant changes in the oral microbiota, with increased colonisation of pathogenic microorganisms and subsequent decline in oral health-related bacteria, which may exacerbate oral complications [7].

Late sequelae of RT include, for example, fibrosis of the masticatory muscles, which can result in trismus [4]. Trismus indicates severely restricted mouth opening, i.e., a mouth opening of 35 mm or less [8] and often progresses during the course of RT and for up to 6 months after start [9]. Osteoradionecrosis, resulting from irradiation of the jawbone, is another severe long-term complication from RT [4], often triggered by periodontal disease and dental extractions [10]. Irradiation of the teeth may also cause damage to hard dental tissue [11].

Together, acute and late sequelae from RT severely impact patients’ ability to sustain dental and periodontal integrity and make those treated for HNC vulnerable to poor oral health. For example, oral mucositis and trismus can impair the patient’s ability to perform oral hygiene and deliver dental care [4, 12]. Radiation-induced damage to dental hard tissues significantly increases the risk of dental caries [4], with an increase in the prevalence of caries over time [13]. Hyposalivation also contributes to poor oral health, as saliva is needed to preserve dental hard tissue integrity, protect the oral tissues, cleanse the oral cavity, and remove food particles [6]. Hence, the multitude of challenges and symptoms arising from HNC treatment that affect the oral cavity may exert a profound influence on the physical functioning and psychosocial well-being of HNC survivors, ultimately compromising overall quality of life.

Many HNC survivors testify that poor oral health is a major and chronic problem that affects many significant aspects of life due to a dry, foul-smelling oral cavity, pain, and missing teeth. Patients also report feeling insufficiently informed about the long-term effects of RT on their oral and dental health [14]. Physical dysfunction, e.g., pain due to mucositis and difficulty swallowing, may increase the risk of disease-related malnutrition [15, 16]. Social aspects can also be affected as some HNC survivors refrain from attending social events and from eating together with others when experiencing problems related to the oral cavity [17]. The numerous oral problems experienced by HNC survivors significantly affect health-related quality of life (HRQoL) [18, 19].

In accordance with standard clinical practice in Sweden, all patients with HNC scheduled to receive RT are routinely invited to undergo an oral health assessment prior to initiation of cancer treatment. Teeth with extensive periapical disease, moderate to severe attachment loss, or severe decay are extracted, and manifest caries lesions are treated. Conventional periodontal therapy is administered if necessary. Standard of care often includes follow-up at a specialist dental clinic for up to approximately three months after treatment. After this, patients are generally advised to visit their own dental clinic, when dental care costs are typically paid for by the patients themselves. Consequently, oral health follow-up for HNC survivors in Sweden lacks consistency and uniformity, and its frequency is variable across healthcare regions. Many patients are unable to afford dental care or choose not to prioritise it. The lack of support and the financial burden associated with dental care for patients with HNC are increasingly recognised within the research community [20, 21]. To support oral health and facilitate early detection of dental caries, patients with HNC should receive a comprehensive oral health care plan with frequent follow-ups over a long period of time after the completion of cancer treatment.

Well-defined, evidence-based guidelines across the healthcare system, including dental services, are essential to support HNC survivors in managing complex oral health challenges. However, there is currently limited evidence regarding how to implement such strategies effectively. This is, therefore, a protocol for a multicentre two-armed randomised controlled trial (RCT) with the aim of evaluating an oral health care programme designed to prevent or mitigate late oral sequalae following completion of HNC treatment, and assessing its impact on HRQoL, oral health, work ability, nutritional status, psychological well-being, and healthcare-related economic costs. Conducting a RCT to test this programme will provide valuable evidence for how structured, evidence-based interventions can be integrated into survivorship care to preserve oral health and improve long-term outcomes. We hypothesise that a clinically structured programme for HNC survivors will significantly improve both oral health and HRQoL.

## Methods

### Study design

We are conducting a multicentre two-armed superiority RCT (ClinicalTrials.gov NCT07173270) and this study protocol outlines the methods that will be used to evaluate the effectiveness of an oral health care programme designed to prevent or reduce late oral sequelae in HNC survivors. The research project has been approved by the Swedish Ethical Review Authority (Dnr 2023-05510-01), with an approved amendment (Dnr 2025-03485-02), and follows the Helsinki Declaration [22]. Written and oral information about the study is given to eligible participants, and written consent is mandatory for participation. This protocol follows the SPIRIT (Standard Protocol Items: Recommendations for Interventional Trials) guideline [23], and the SPIRIT checklist can be found as a supplement (Supplementary A).

### Participants

Patients diagnosed with HNC are randomly assigned in a 1:1 ratio to either an oral health care programme (intervention) or standard of care. The power analysis was performed based on data from a prospective observational study on HNC (ClinicalTrials.gov NCT03343236) involving individuals with various HNC diagnoses. In that study, we collected data using the European Organisation for Research and Treatment of Cancer Quality of Life Questionnaire – Head and Neck Module (EORTC QLQ-H&N35) [24]. Data from this instrument, specifically the ‘Dry mouth component’ of the EORTC QLQ-H&N35, form the basis for the power calculation, assuming a mean of 52 and a standard deviation (SD) of 33 after one year in the standard of care group.

Sample size was determined using simulation-based power calculations for an ANCOVA model, adjusting for baseline values, with robust standard errors. Simulations enable a skewed outcome bounded between 0 and 100 and a conservative zero correlation between baseline and follow-up. Simulation-based power calculations were chosen due to the discrete and bounded nature of the outcome variable, which violates the assumptions underlying standard normal-theory sample size formulas.

A total of 250 participants (125 per group) provides approximately 80% power to detect a clinically relevant difference of 10 units between groups at a two-sided 5% significance level. To account for potential dropouts, we plan to enrol 300 patients in total that will be randomised. Calculations were performed using R version 4.3.3.

Inclusion started in September 2025. Patients are recruited at different hospitals in Sweden. Clinical/research nurses at each cite identify eligible patients in relation to a multidisciplinary conference, where treatment options for newly diagnosed patients with HNC are discussed and planned. Informed consent is obtained from the participant by the clinical/research nurses. The number of patients who decline participation or who are inadvertently omitted from being approached is documented in the research database Research Electronic Data Capture (REDCap) [25].

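### The stated 80% power for 125 per group does not follow from the stated inputs; with SD 33 in both arms it is about 67%

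*Protocol article*

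**What the plan says.** The calculation is in the protocol article under Methods, Participants. It uses the dry mouth component of the EORTC QLQ-H&N35 from an earlier observational cohort, "assuming a mean of 52 and a standard deviation (SD) of 33 after one year in the standard of care group". The method is described as "simulation-based power calculations for an ANCOVA model, adjusting for baseline values, with robust standard errors". On the shape of the outcome and the covariate the text says: "Simulations enable a skewed outcome bounded between 0 and 100 and a conservative zero correlation between baseline and follow-up". Simulation is justified because the outcome is discrete and bounded, so standard normal-theory formulas are said not to apply. The result is: "A total of 250 participants (125 per group) provides approximately 80% power to detect a clinically relevant difference of 10 units between groups", for a two-sided 5% test. For dropout, "we plan to enrol 300 patients in total that will be randomised".

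The section gives no SD or distribution for the intervention arm and no dropout rate.

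**The concern.** The printed inputs are nearly enough to recompute the power, and a quick check falls well short of 80%. A zero correlation means that the baseline covariate removes no residual variance, so the ANCOVA has the precision of a plain comparison of two means. The control SD of 33 comes from a 0-100 scale, so it already reflects the bounds.

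This paragraph is the only quantitative justification of the trial's size in the article. If power under the stated conditions is about 67%, the chance of missing a true 10-unit benefit is about 1 in 3, where the text implies 1 in 5. A null result would then be read as stronger evidence against a 10-unit effect than it is.

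**Working it through.** **Inputs, all from Methods, Participants:** control mean 52 and SD 33; difference 10; two-sided 5%; 125 per group analysed; zero correlation with baseline; ANCOVA with robust standard errors. **Assumption, not in the document:** intervention-arm SD also 33.

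**1. Attempt to reproduce the stated 80%.**
- SE = 33 × √(2/125) = 4.174
- 10 / 4.174 = 2.396
- Power = Φ(2.396 − 1.960) = Φ(0.436) ≈ 0.67 (noncentral t: 0.665)

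The stated figure is not reproduced; the gap is about 13 percentage points.

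**2. All 300 analysed, no losses (150 per group).**
- SE = 33 × √(2/150) = 3.811
- Power = Φ(10/3.811 − 1.960) = Φ(0.664) ≈ 0.747 (noncentral t: 0.744)

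**3. Does a discrete or bounded outcome change the answer?** ANCOVA with HC3 robust standard errors and an independent baseline was simulated with 5,000 to 10,000 runs per setting. The group means were 52 and 42, and the SDs were 33 or close to it.
- Four-level outcome (0/33/67/100), proportional-odds shift, intervention SD 32.6: 66.0% at 125 per group, 74.2% at 150.
- Four-level outcome, SD 33 in both arms: 65.1% and 74.2%.
- Continuous beta outcome on 0-100, SD 33 in both arms: 65.4% and 72.7%.
- Repeat runs of the four-level and beta settings gave 66.1-66.8% at 125 per group, and 73.9% where 150 per group was also run.

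At this sample size the test depends almost entirely on the mean difference and the two SDs, so the results stay close to the formula.

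**4. What would give 80% at 125 per group?** The required SE is 10/(1.960 + 0.842) = 3.569.
- Common SD: 3.569 / √(2/125) = 28.2 in both arms, against the stated 33 in control.
- Intervention SD alone, control held at 33: √(125 × 3.569² − 33²) ≈ 22.4.
- Correlation: √(1 − (28.22/33)²) ≈ 0.52, against the stated zero.
- Difference: 2.802 × 4.174 ≈ 11.7 units, against the stated 10.
- A one-sided 5% test would still give only Φ(2.396 − 1.645) ≈ 77.4%, and the text specifies a two-sided test.

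**5. Range over the unstated input.** Power = Φ(10 / √((33² + s²)/n) − 1.960), where s is the intervention-arm SD:

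| s | 125 per group | 150 per group |
|---|---|---|
| 33 | 66.8% | 74.7% |
| 30 | 70.8% | 78.4% |
| 28 | 73.3% | 80.8% |
| 25 | 77.1% | 84.1% |
| 22.4 | 80.0% | 86.7% |

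**6. Size needed for 80% with SD 33 in both arms:** 2 × 33² × 2.802² / 10² ≈ 171 per group, or 342 analysed.

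**The case against.** The strongest reply is that SD 33 is stated for standard of care only. The intervention-arm distribution used in the simulation is not given, so strictly the printed inputs do not exclude 80%. This stands, and a consistent example can be built. On the four-level scale, take control probabilities 0.12/0.447/0.186/0.247 (mean 52, SD 33) and intervention probabilities 0.12/0.50/0.38/0 (mean 42, SD 21.9). Then 10/√((33² + 21.9²)/125) = 2.82, and power is about 80.6%. A reader might therefore go too far in concluding that the 80% is proven wrong because every input is printed; one input is not.

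The example is extreme, however. It empties the worst category entirely and cuts the SD by a third in one arm. For the four-level control distribution used in step 3, the most variance-reducing shift that makes no score worse (SD 24.1) gave only 77.6% in simulation. An ordinary proportional-odds shift leaves the SD near 33. Nothing in the article declares such a contraction.

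A second reply is that zero correlation is called conservative, so actual power may be higher. With 150 per group and SD 33 in both arms, a correlation of 0.3 gives about 79% and 0.4 about 82%. That is fair as a statement about the trial, but the 80% is claimed at zero correlation with 250 participants, and the document reports no correlation.

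Two further inferences are not supported. A reader might guess that the simulation lost variance when draws were forced into the 0-100 range, but the code is not described and no cause can be identified. A reader might also count losses before the 6-month randomisation against the 50-patient allowance, but the text says that the 300 are patients who will be randomised.

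**Conclusion.** The concern holds as a failure of the stated power to follow from the stated inputs. With a 10-unit difference, a two-sided 5% test, zero correlation and SD 33 in both arms, 125 per group gives about 67% and 150 per group about 75%, against the 80% claimed for 125. The appeal to a bounded, discrete outcome does not account for the difference.

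The result rests on one assumption, the intervention-arm SD. The shortfall closes only if that SD is about 22.4, which is neither stated nor justified. The 1-in-3 risk of missing a true effect likewise applies at 125 per group, equal SDs and zero correlation, and would be smaller if any of these were more favourable.

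**What to change.** Rerun the simulation and check that its realised control mean, control SD and group difference are 52, 33 and 10. State the intervention-arm SD or distribution that was used.

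Unless a much smaller intervention-arm SD is declared and justified, restate the result along these lines: with 250 participants analysed and no baseline correlation, power is about 67% for a 10-unit difference, and 80% for about 11.7 units. If credit is wanted for a positive correlation, take its value from the observational cohort and declare it in the same paragraph.

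The cost is one simulation and one corrected paragraph, plus any other place where the figure is repeated. No extra patients are needed for the correction. The downside is a less favourable stated power.

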#### Inclusion and exclusion criteria

The inclusion criteria are patients (≥ 18 years) planned for HNC treatment with curative intent, i.e., RT with or without systemic anti-cancer therapy, SACT (e.g., chemotherapy, immune therapy, targeted therapy) and/or surgery. Tumour sites include the oral cavity, oropharynx, larynx (only stage III and IV), hypopharynx, nasopharynx (squamous cell carcinoma), salivary glands, or unknown primary. The exclusion criteria are patients with severe alcoholism, cognitive impairment, or inability to understand the Swedish language.

### Allocation and follow-up

Patients are followed from baseline (before the start of cancer treatment) and at 4 subsequent follow-ups: 6 months after completion of treatment, and 1, 2, and 3 years after the 6-month follow-up (Fig. 1).

**Fig. 1 Fig1:**
[figure not shown]
Follow-up and randomisation to the intervention; an oral health care programme. Created in BioRender. [name] (2026) https://BioRender.com/v8xvrby

Standard of care, according to clinical practice in Sweden, is provided to all participants for up to approximately 3 months after treatment. At the 6-month follow-up, patients are randomised (1:1) to receive either the intervention (oral health care programme) or standard of care. A statistician has generated the randomisation list; no members of the research team were involved in this process or have access to the randomisation list. Randomisation is computer-generated using REDCap.

### Intervention and standard of care

The oral health care programme is a practice-led intervention that was developed by a multidisciplinary team of healthcare professionals and researchers (physicians, nurses, dentists, dental hygienists, and a dietitian), and in close collaboration with HNC survivors. The intervention starts 6 months after completion of RT and ends after the 3-year follow-up. Every 3 months, participants in the intervention group are scheduled for an appointment with a dental hygienist. During these visits, participants are asked about oral hygiene habits, fluoride use, dietary habits (with focus on intake of easily degradable carbohydrates), and oral dryness. The dental hygienist also performs a thorough examination of the oral cavity, assessing signs of dental problems (e.g., tooth decay) or gum problems (e.g., gingivitis or periodontitis).

The intervention is individually tailored and based on the examination and the patient’s report. It includes oral and written advice, and recommendations from the dental hygienist, e.g., how to increase oral hygiene using the correct toothbrushing technique, interdental cleaning, or strategies to address oral dryness. It also includes tailored preventive professional oral hygiene treatment, e.g., plaque and dental calculus removal, fluoride gel application, and polishing to produce a smooth and clean surface. All visits to the dental hygienist are at no cost. If oral problems are beyond the competence of the dental hygienist, dentists are consulted and the participant pays for any necessary treatment.

At the 6-month follow-up, patients are randomised to receive the intervention (oral health care programme) or standard of care, which in Sweden only includes dental care for up to approximately 3 months following treatment. Within standard of care, patients therefore need to actively seek dental care and support themselves after 6 months. Patients who have undergone RT targeting the oral cavity may be entitled to a partial allowance, which subsidies preventive dental care; however, not all patients receive this benefit, and it does not cover all the costs.

### Data collection

#### Primary and secondary outcome measures

The primary outcome measure is HRQoL. Secondary outcome measures are: Quantitative oral health indicators, return to work (sick leave), nutritional status, healthcare-related economic costs, and patient-reported outcome measures (PROMs) focusing on self-reported oral health, psychological well-being (depression, anxiety and stress), and self-efficacy.

